
### Data analysis and interpretation of results

As part of Objective 1, a mapping of the care pathways encountered will be completed for each type of MSKD encountered in our study population (i.e., low back pain, neck pain, upper limb, lower limb) (Fig 1). The unit cost of each of the resources, consumables and indirect costs required in each process of care of the care pathway will be calculated and multiplied by the duration of each process to obtain the cost related to each process of care present in the care pathway. The costs associated with each process will be summed to obtain the total cost of the ED care pathway specific to each MSKD and each model of care (i.e., emergency physician or primary contact physiotherapist and emergency physician management). A generalized linear model with a Gamma distribution and log link will be used to test whether there is a significant difference in the costs of managing equivalent MSKDs between the two models of care [52, 53].

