## Materials and methods

### Study design and costing approaches

This study is composed of three distinct designs, one per objective. The costing approach used for Objective 1 will be Time-Driven Activity-Based Costing (TDABC), which involves determining the per-minute costs associated with each care process included in a care pathway by multiplying the cost per minute of each care process by its duration. Details on this costing approach and its application to the ED have been described by one of the authors elsewhere [36]. Objective 2 will be achieved through a cost-utility analysis approach in which health care costs at the ED visit and those reported at the 1- and 3-month follow-ups will be compiled and combined with the utility scores obtained at the same measurement times, from both Health system and Societal perspectives. Cost-utility analysis is favored in Canada since it uses a generic outcome measure allowing comparison of the health gains associated with several different interventions, such as different models of care [35].

The ICER between the three ED models of care for the management of MSKDs over a two-year period (Objective 3) will be estimated using a cost-effectiveness analysis via a hybrid mathematical model. This model will consist of a decision tree covering the period from the initial ED visit up to three months post-initial visit, and a Markov model starting three months post-initial ED visit and ending 24 months (two years) after the ED visit. The decision tree provides a simple and clear illustration of a patient’s possible short-term care pathways following a new intervention [35, 37]. In addition to reporting the different interventions used, the decision tree also allows for the inclusion of adverse events following the initial intervention, such as a new ED visit for the same condition, and for repeating an intervention over time as needed (e.g., new visit in the ED a few days after the initial visit and then a new visit two months later for the same condition) [35, 37]. It also permits to determine the proportion of disability associated with each of the three ED models of care.

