### Study outcomes

Primary outcomes used to measure the average cost of an ED visit (Objective 1) will be the costs of care processes and the time associated with each care process. This method of costing is routinely used by some members of the research team [36, 45, 46]. The costs related to ED management (medical and non-medical staff, imaging, medication, consumables, maintenance, etc.) were obtained via a formal request made by a member of the research team to the CHU de Québec–UL Finance Department. The time associated with each care process was calculated by a member of the research team using estimates provided by the CHUL medical and non-medical staff that were validated during an observation period in the ED [36, 45]. Uncertainty in measured times will allow the variability of ED costs to be considered, and to derive a distribution of possible costs at baseline for each participant.

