As part of the cost-utility analysis (Objective 2) and hybrid mathematical model (Objective 3), the efficiency of the ED models of care will be assessed using an incremental cost-effectiveness ratio (ICER). The resulting ICER will be reported in terms of incremental cost per quality-adjusted life years (QALY) gained, between the models of care. The follow-up costs of each participant recorded via the self-administered follow-up questionnaires completed at 1 and 3 months during the pilot pragmatic RCT will be added to the distribution of ED visit costs for each individual obtained under Objective 1. Once all costs have been added, an average will be calculated to obtain an average cost per participant at 3 months, for each model of care (Objective 2 & 3 –decision tree). The questionnaires provided data on resources used by each participant during follow-up such as ED re-visits for the same condition, number of consultations with other health professionals in the public and private sector, imaging tests used, etc. The costs of all resources used in the public healthcare system will be drawn from public cost repositories data from the *Régie de l’assurance-maladie du Québec* (RAMQ) (costs related to the emergency physician and other physicians consulted, drugs, laboratory analysis, imaging tests) [47]. Hourly rates for the primary contact physiotherapist and other health professionals consulted (e.g., massage therapist, chiropractor, osteopath) will be derived from a search of the grey literature and will be based on rates in effect within the private healthcare system, since the majority of these professionals work within this system [47]. Costs related to the use of technical aids (e.g., cane, crutches, walker) will also come from a grey literature search. It should be noted that the salary data available from human resources for all healthcare professionals (physicians and allied health professionals) considered will not allow for variability in hourly costs. The only source of variability considered for the purpose of these analyses will be that related to the time required for ED processes. Utility scores were obtained at the initial visit [48] and at 1 and 3 months using the EQ-5D-5L, a generic standardized questionnaire designed to measure health status in an economic and clinical evaluation [49]. The EQ-5D-5L has been found to be reliable, valid, and sensitive to change [50, 51]. The difference in utility scores between the 3-month follow-up and baseline will be calculated for each participant using area-under-the-curve analyses. Once the difference in utility scores will be calculated for each participant, the differences will be averaged to obtain the average gain or loss in utility scores per ED care model. The mean gain or loss in utility scores will then be transformed into QALYs. The efficiency values and the costs from 3 to 24 months required to run the Markov model (Objective 3) for the three models of care will be taken from the literature.

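### The Objective 1 costing rule multiplies consumable costs by process duration, so per-item costs rise with minutes and can bias the ED cost comparison

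*Protocol article*

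**What the plan says.** The section on data analysis and interpretation of results gives the costing rule for Objective 1. Resources come first in the sentence, which continues: "consumables and indirect costs required in each process of care of the care pathway will be calculated and multiplied by the duration of each process". The section on study design and costing approaches defines the method in the same way, as "multiplying the cost per minute of each care process by its duration". The article states no separate quantity-times-price term for inputs used during the ED visit.

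Under study outcomes, the ED costs obtained from the Finance Department cover "medical and non-medical staff, imaging, medication, consumables, maintenance, etc". That list mixes time-driven inputs with inputs priced per unit. Process times were derived "using estimates provided by the CHUL medical and non-medical staff that were validated during an observation period in the ED". Uncertainty in those times is to give each participant a distribution of baseline costs, and "The only source of variability considered for the purpose of these analyses will be that related to the time required for ED processes".

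The process costs then go into three steps:
- **Pathway total:** "The costs associated with each process will be summed to obtain the total cost of the ED care pathway specific to each MSKD" and to each model of care.
- **Objective 1 test:** "A generalized linear model with a Gamma distribution and log link will be used to test whether there is a significant difference" in cost between the two models.
- **Objectives 2 and 3:** participants' follow-up costs "will be added to the distribution of ED visit costs for each individual obtained under Objective 1".

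**The concern.** One multiplier is applied to inputs that behave differently. A clinician's time, and the room and overhead that go with it, cost more when a process takes longer. A dressing or a splint costs the same whether the encounter takes 20 minutes or 30. Multiplying consumables by duration gives them a charge that follows the clock instead of the quantity used.

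Two things are at stake:
- **Mean cost.** Where the same process takes longer under one model of care, that model is charged more for the same items. The Objective 1 comparison, and the cost difference in the ICER, would then include a component that is not resource use.
- **Spread.** Because process time is the only source of variability considered, each participant's cost distribution would include variation in item costs that have no dependence on time. The variation that does exist, in how many items were used, would not be represented.

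**Working it through.** The article states no unit cost, process duration or consumable share, so there is no figure of its own to reproduce. The check compares costing rules algebraically and then with assumed inputs.

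**Set-up.** One process uses the same item in both arms. Let r be the staff and overhead rate per minute (equal in both arms), t the duration in minutes and C the cost of the item.

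- Item counted once: cost = r × t + C
- Item spread as a common per-minute rate q: cost = (r + q) × t

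**Illustration (all figures assumed).** r = 2 per minute, C = 10, durations 20 and 30 minutes, q = 10 / 25 = 0.40 (item cost over the mean duration).

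| Rule | Shorter arm | Longer arm | Difference | Ratio |
|---|---|---|---|---|
| Item counted once | 2 × 20 + 10 = 50 | 2 × 30 + 10 = 70 | 20 | 1.40 |
| Common per-minute rate | 2.40 × 20 = 48 | 2.40 × 30 = 72 | 24 | 1.50 |

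The same item is charged 0.40 × 20 = 8 in one arm and 0.40 × 30 = 12 in the other. The same spread appears within an arm if the uncertainty about one process runs from 20 to 30 minutes, although the item always costs 10.

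Two boundary cases:
- **Equal durations (20 and 20 minutes).** Both rules give 50 and 50, a ratio of 1.00.
- **Rate calibrated to each arm's own time.** The rates are 10/20 and 10/30 per minute. Costs are 50 and 70, so the means are correct and only spurious variability remains. The article does not describe such a rate.

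**General form.** Let A be the shorter arm's process cost, s the share of A that is consumables, and R the ratio of the longer to the shorter duration. Set the per-minute rate so that it reproduces A in the shorter arm.

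- Difference with items counted once: A × (1 − s) × (R − 1)
- Difference with items scaled by time: A × (R − 1)
- Inflation of the difference: 1 / (1 − s), whatever R is, provided R is not 1
- Cost ratio with items counted once: (1 − s) × R + s; with items scaled by time: R

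With R = 1.25 (assumed):

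| Assumed s | Inflation 1/(1 − s) | Ratio, counted once | Ratio, scaled by time |
|---|---|---|---|
| 5% | 1.05 | 0.95 × 1.25 + 0.05 = 1.238 | 1.25 |
| 10% | 1.11 | 0.90 × 1.25 + 0.10 = 1.225 | 1.25 |
| 20% | 1.25 | 0.80 × 1.25 + 0.20 = 1.20 | 1.25 |

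**Direction.** The spurious amount is q × (difference in minutes), so it always adds cost to the arm with the longer process. The table assumes equal staff rates. If the longer process were the cheaper one, because of a lower staff rate, the same amount would narrow the difference instead of widening it.

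**The case against.** The strongest case on the other side has four parts.

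- **No durations by arm.** Bias in the comparison needs the same process, with the same item, to last longer in one arm, and the article does not say this. The arms may differ mainly in which processes occur, since one arm adds a physiotherapist to the physician. The introduction cites shorter waits and stays under physiotherapist care. That makes differing durations plausible but does not establish them for any given process. This part stands. A reader might infer that the ED comparison is definitely distorted; the document does not support that.
- **Unit cost may already be per minute.** A reader might take the rule to multiply an item's price directly by minutes, which would be dimensionally wrong and grossly inflate costs in both arms. The design section defines a cost per minute for each process, so that reading is the less plausible one, and nothing here rests on it. The milder reading still scales item costs with time, and the article gives no derivation of a per-minute consumable rate.
- **Drugs and imaging are not named in the rule.** It names resources, consumables and indirect costs. Imaging and medication fall under it only if they count as resources. The pharmacy transactions and drug cost repository listed under data collection suggest that drugs may be costed by item. So the point is firm for consumables and conditional for the rest.
- **A condensed article.** Details of the costing are referred to a cited paper, and the figure mapping the pathway is not shown here. The sentence may be shorthand for a sounder method. That lowers confidence that the actual calculation is wrong. It does not make the stated rule right, because this is an explicit formula and not an omitted detail.

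**Conclusion.** The costing rule as written is wrong for consumables: it makes a per-item cost proportional to minutes and subjects it to time uncertainty. It can bias the Objective 1 cost comparison, and through the ED costs also the ICERs of Objectives 2 and 3.

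Neither the presence, the direction nor the size of a between-arm bias is shown. Under the assumed consumable shares of 5% to 20%, with equal staff rates and a rate that reproduces the shorter arm's cost, a duration-driven difference is inflated by a factor of about 1.05 to 1.25. At the low end this is minor: a cost ratio of 1.25 instead of 1.238 when one duration is a quarter longer. With equal durations and identical use, the ratio does not change. The correction is worth making because it is cheap and because the same ED costs serve all three objectives.

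**What to change.** Restate the rule in the section on data analysis and interpretation of results as two terms:

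ED cost per participant = sum over processes of (staff and indirect cost per minute × minutes) + sum over items of (quantity used × unit price).

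The second term holds consumables, and any imaging, laboratory tests or medication that would otherwise be treated as resources under the duration rule. Align the definition in the section on study design and costing approaches with this.

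Quantities can come from the patient record and the ED pharmacy transactions. Prices can come from the drug costs repository, the public price lists and the Finance Department costs. All of these are already named in the article. Apply the uncertainty in process times only to the first term.

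If the working method already does this, one clarifying sentence is enough. The cost is one changed formula in the protocol and the costing spreadsheet, and slightly more data handling for itemised inputs. No new data source is needed.

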### Population of interest

Inclusion and exclusion criteria for the population of interest are described in Box 1. The population targeted covers persons with a peripheral or spinal MSKD, a P3, P4 or P5 triage category at the ED (Canadian Triage and Acuity Scale [43]), and that are aged between 18 and 80. Having a major MSKD, red flag or associated unstable condition are criteria for exclusion.

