### Data collection

Objectives 1, 2 and 3 will be achieved in part using data collected through a two-arm pilot pragmatic randomized clinical trial (RCT) conducted in the ED of the CHUL, one of the five sites of the CHU de Québec—Université Laval (UL) (Quebec City, Canada) from September 2018 to March 2019 (n = 78). This trial aimed to compare the effects of management by a primary contact physiotherapist to usual care provided by an emergency physician for persons presenting with a minor MSKD on their clinical course (pain and pain interference) and the use of resources at ED discharge and after 1 and 3 months post-visit [29]. Two groups of participants were compared: one group managed by a primary contact physiotherapist and an emergency physician and one group managed by an emergency physician alone.

Data were collected at the initial ED visit and at the one- and three-month post-visit follow-ups. While more details of the data collection procedures can be found in our previous paper [29], any person presenting to the ED who met the inclusion and exclusion criteria was seen by a member of the research team who confirmed eligibility, obtained informed consent, and ensured completion of baseline questionnaires. The participant was then randomized to either study group: primary contact physiotherapist + emergency physician management or usual management by the emergency physician alone. After the ED visit was completed, participants were contacted at 1 and 3 months either by phone or email to complete post-visit follow-ups. The supplementary data needed to meet the three Objectives will come from some of the CHU de Québec—UL administrative databases (nominative data: SIURGE (ED management software), Cristal-Net (patient electronic record), and the CHUL’s ED pharmacy transactions directory; administrative data: prescription and over-the-counter drug costs repository), the scientific literature, and public cost repositories (e.g., salaries of general practitioners and specialists, see https://www.msss.gouv.qc.ca/inc/documents/ministere/acces_info/seance-publique/etude-credits-2018-2019/Reponses-aux-questions-generales-et-particulieres-RAMQ.pdf; laboratory analysis costs, see https://publications.msss.gouv.qc.ca/msss/fichiers/2017/17-922-05W.pdf).

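### Adjusting the Objective 1 cost model for triage category would be a cheap gain in precision; leaving it out is not a source of bias

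*Protocol article*

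**What the plan says.** All places are in the protocol article.

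- **Population of interest.** Eligible patients have "a P3, P4 or P5 triage category at the ED". Severity is also capped: "Having a major MSKD, red flag or associated unstable condition are criteria for exclusion".
- **Data collection.** Eligibility was confirmed and baseline questionnaires were completed first. Then: "The participant was then randomized to either study group". Triage category, as an entry criterion, is therefore fixed before allocation and should be held for everyone. Recruitment ran from September 2018 to March 2019 (n = 78).
- **Data analysis and interpretation of results.** Pathways are mapped "for each type of MSKD encountered in our study population (i.e., low back pain, neck pain, upper limb, lower limb"), and the costs are summed to give "the total cost of the ED care pathway specific to each MSKD and each model of care". The comparison is by a Gamma model with log link, and its stated purpose is to "test whether there is a significant difference in the costs of managing equivalent MSKDs between the two models of care". The article does not define what makes two disorders equivalent, and it names no covariate for the model. The planned subgroups are sex and MSKD category, not triage.
- **Study outcomes.** Each participant's follow-up costs are added to that person's distribution of ED visit costs. The totals are then averaged within each care model to give the 3-month cost for Objective 2 and the decision tree.

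**The concern.** The contrast in Objective 1 rests on comparing like with like, and body region is the only grouping offered to give that idea content. On that grouping, a P3 and a P5 low back pain fall in the same cell. Time-driven costing prices staff time, imaging and medication, and it is plausible that these vary with triage category. If they do, triage is a baseline predictor of the outcome that costs nothing to use.

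Two things are at stake. With 78 patients, unexplained variation in cost between triage levels widens the interval around the cost ratio. And recruitment is over, so the arms have already ended up with some particular triage mix. An estimate that ignores triage takes that mix as it is, and choosing to adjust only after seeing it would be a data-driven decision. The 3-month cost in Objective 2, described as a plain arm average, is exposed in the same way.

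**Working it through.** The article gives no power or precision figure for Objective 1, so there is none to reproduce. The check asks what omitting triage does to bias, error rate and precision.

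**Inputs.** From the article: 78 participants, randomised, Gamma model with log link, triage P3 to P5. Assumed, because the article does not give them: 39 per arm; two-sided 5% level; triage split 30/50/20 for P3/P4/P5; a constant cost ratio r between adjacent levels of 1.2, 1.5 or 2.0; within-level coefficient of variation (CV) 0.4. The value r = 2.0 makes P3 four times as costly as P5 and serves as an extreme.

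**1. Size of chance imbalance.** The standard deviation of the between-arm difference in a share p is √(2p(1−p)/n). At 39 per arm:
- p = 0.2: √(2 × 0.16/39) = 0.091
- p = 0.5: √(2 × 0.25/39) = 0.113

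At about 10 per arm, as might apply within one region, the values are 0.179 and 0.224. Differences of 10 points or so overall are ordinary.

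**2. Bias and overall error rate.** Gamma log-link models were simulated with no true difference (2,000 runs per setting; Monte Carlo error of a 5% rate is about √(0.05 × 0.95/2000) = 0.5 points).
- Without triage, the mean log cost ratio lay between −0.006 and +0.003 across settings. Rejection was 5.4–5.8% at 39 per arm and 5.4–6.4% at 10 per arm.
- With triage, rejection at 39 per arm was 4.9–6.1%.

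So there is no bias and no material inflation in either analysis.

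**3. Precision.** The standard deviation of the log ratio is about √(2 × CV²/39).
- Within triage levels: CV² = 0.16, giving √(0.32/39) = 0.091.
- Ignoring triage, CV² = 1.16 × E(m²)/E(m)² − 1, where m is the relative mean cost by level (r, 1, 1/r).
  - r = 1.2: 1.16 × 1.0709/1.0267² − 1 = 0.179, standard deviation 0.096
  - r = 1.5: 1.16 × 1.2639/1.0833² − 1 = 0.249, standard deviation 0.113
  - r = 2.0: 1.16 × 1.75/1.2² − 1 = 0.410, standard deviation 0.145

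The simulation gave 0.096, 0.115 and 0.146 unadjusted, against 0.092–0.094 adjusted, in agreement.

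**4. Power for a 20% lower cost** (log 0.8 = −0.223), simulated, adjusting for all three triage levels:

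| r | Unadjusted | Adjusted |
|---|---|---|
| 1.2 | 64% | 67% |
| 1.5 | 49% | 68% |
| 2.0 | 34% | 67% |

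**5. Collapsing triage to P3 versus P4/P5.** This split keeps part of the gain. At r = 1.5, the merged P4/P5 group has CV² = 1.16 × 0.8413/0.9048² − 1 = 0.192. The average over the two groups is 0.3 × 0.16 + 0.7 × 0.192 = 0.182, and the standard deviation is √(2 × 0.182/39) = 0.097. Power is about Φ(0.223/0.097 − 1.99) = Φ(0.31), or 62%, between the 49% and 68% above. At r = 1.2 the loss from collapsing is negligible.

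**6. Given a large realised imbalance.** In the 10% of null runs with the largest P3 gap (18 points or more at 39 per arm), the false-positive rate was 7%, 15% and 23% unadjusted for r = 1.2, 1.5 and 2.0, against 5–6% adjusted.

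**The case against.** A reader might infer that a chance difference in acuity will be read as a cost difference between care models. The documents do not support that. Allocation was random, and the standard error and the 5% level already allow for chance imbalance in triage; steps 2 and 3 bear this out. The raised false-positive rates in step 6 apply only to the most unbalanced tenth of possible allocations, and nothing in the article shows that this trial is one of them.

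A reader might also infer that the plan defines equivalence by body region alone and fits an unadjusted model. It says neither. Region is the only grouping shown, but the term is left undefined, and a condensed article may leave the covariate list to a fuller plan. Silence on covariates is therefore not an error in itself.

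Nor does the Objective 1 contrast carry into Objectives 2 and 3. Those use individual costs averaged by arm, so a covariate added to the Objective 1 model would leave them unchanged. The Objective 2 bootstrap already carries sampling variation in case mix.

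Finally, the article gives neither the triage mix nor cost by triage level. The exclusion of major disorders and red flags narrows the spread of severity, and the Discussion already asks for caution because of the small sample. At r = 1.2 the gain in power is only three points.

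All of this stands. It removes any claim of bias and leaves the size of the gain unknown. It does not remove the case for using a pre-randomisation variable that is already held and plausibly predicts the outcome.

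**Conclusion.** The point holds as a minor improvement in efficiency. The unadjusted comparison is valid on average. If triage predicts ED cost, adjusting for it keeps the error rate near 5%, narrows the interval and protects against the imbalance that has already occurred, whatever its size. With three-level adjustment, the illustrative gain in power is 3 points (64% to 67%) at an adjacent-level cost ratio of 1.2 and 19 points (49% to 68%) at 1.5. With the P3 versus P4/P5 split, the latter is about 13 points (49% to 62%). These figures rest on assumed arm sizes, triage split, cost ratios and within-level CV, none of which the article supplies. If triage predicts cost only weakly, the gain is close to nil.

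**What to change.** In the data analysis section, define what makes disorders equivalent. State that the Objective 1 Gamma, log-link model is fitted once on all 78 participants with care model, triage category (P3 versus P4/P5) and body region as baseline covariates, and that the adjusted mean cost difference is reported. Fix this before costs are examined by arm.

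Objective 2 needs its own sentence. Apply the same covariates to the 3-month cost comparison, refitted within each resample of the planned bootstrap, in place of the plain arm average described under Study outcomes.

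The cost is a sentence or two and no new data. The covariates take about four degrees of freedom (one for triage, three for the four body regions), so residual degrees of freedom go from 78 − 2 = 76 to 78 − 6 = 72. Collapsing P4 and P5 saves one degree of freedom and gives up some precision if those two levels differ clearly in cost.
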